#### **6.3.3.B COMPARISON: RT+STHT vs RT+LTHT**

##### **Original power calculations:**

It was estimated that DSS would be 87% at 10 years in patients on the STHT arm. This is lower than the estimated 91% 10-yr DSS in the research arm (STHT) in the previous comparison if STHT is more effective than no-HT, as we anticipate that higher risk patients will enter the STHT vs LTHT comparison. This superiority trial is testing whether the LTHT can improve disease-specific survival to 93% at 10 years (hazard ratio HR=0.52). A total of 1077 patients (91 events) in a comparison of STHT vs LTHT would allow for 80% power to detect an increase in 10-year DSS of 6% with a 3% significance level (accounting for the multiple use patients who join the three-way randomisation). This assumes that 30% of patients are lost to follow-up.

This could be achieved in 51/2 years with 26 patients randomised each month from 30 months onwards. Patients would be followed-up for 7 years after the end of recruitment. The numbers above allow for a certain percentage of patients to be lost to follow-up.

If the peak accrual is lower, at around 20 patients per month, accrual would be extended by 1 year to around 6.5 years and around 1129 patients would be randomised; this should address the question in the same timescale with the same power.

### Updated power calculations:

The primary outcome measure of RADICALS-HD was amended from DSS to MFS after peer review in 2019 and without any reference to accumulating, comparative data. At this point, recruitment was already completed with 1524 patients in the 6 vs 24 months comparison. It is estimated that MFS will be approximately 75% at 10 years in patients allocated to the 6-month group of the 6 vs 24 months comparison; it is expected that patients in this comparison will be at higher risk of an event than those in the 0 vs 6 months comparison. The 6 vs 24 months comparison should have over 80% power, with a two-sided 5% alpha, to detect an absolute increase in MFS of 6%, from 75% in the short-HT group to 81% in the long-HT group (HR=0.72). Approximately 300 MFS events are anticipated for this analysis.

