##### **Updated power calculations:**

The primary outcome measure of RADICALS-HD was amended from DSS to MFS after peer review in 2019 and without any reference to accumulating, comparative data. At this point, recruitment was already completed with 1480 patients in the 0 vs 6 months comparison. It is estimated that MFS will be approximately 80% at 10 years in patients allocated to the no-HT group. The 0 vs 6 months comparison would have over 80% power, with a two-sided 5% alpha, to detect an absolute increase in MFS of 6%, from 80% in the no-HT group to 86% (HR=0.67) in the short-HT group. Approximately 200 MFS events are anticipated for this analysis.

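### In 6.3.3.B, 10-year MFS of 75% to 81% is HR 0.73, not 0.72, so about 300 events give 76-77% power rather than over 80%

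*Combined protocol and SAP*

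**What the plan says.** The updated power calculation in section 6.3.3.B covers short-term v long-term hormone therapy, with 1524 patients already recruited:

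- On the control arm: "It is estimated that MFS will be approximately 75% at 10 years in patients allocated to the 6-month group".
- On power: "The 6 vs 24 months comparison should have over 80% power, with a two-sided 5% alpha".
- On effect and events: "from 75% in the short-HT group to 81% in the long-HT group (HR=0.72). Approximately 300 MFS events are anticipated for this analysis".

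The updated calculation in 6.3.3.A covers no v short-term hormone therapy and has the same form, again claiming over 80% power at two-sided 5%: "from 80% in the no-HT group to 86% (HR=0.67) in the short-HT group. Approximately 200 MFS events are anticipated for this analysis".

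Section 6.3.1 sets the smallest effect of interest in RADICALS-HD as an absolute gain of 6 points in 10-year MFS. Section 6.5 names the log-rank test for the main outcomes.

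**The concern.** The 6.3.3.B statement gives the effect twice, as a pair of survival rates and as a hazard ratio, and the two do not agree. The printed HR is the more favourable one. If the target is the 6-point gain, as 6.3.1 says, the stated power is not what the plan's own rates and event count deliver. This is one of the two main RADICALS-HD comparisons, and the figures form part of the case for changing the primary outcome to MFS. With recruitment closed, the number of events at analysis is the main determinant of power still open, so readers should know what 300 events provide.

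**Working it through.** **Inputs.** 10-year MFS 75% and 81%, HR 0.72, about 300 events and two-sided 5% alpha are from 6.3.3.B. The log-rank test is from 6.5. Equal allocation within the pair is assumed, in line with the 1:1:1 in the Trial Summary.

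**Formulas.**
- HR from survival rates under proportional hazards: ln(S1)/ln(S0)
- Schoenfeld power: Φ(½√d · |ln HR| − 1.96)
- Freedman power: Φ(√d · (1 − HR)/(1 + HR) − 1.96)

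**Step 1: reproduce the plan's figure with its printed HR of 0.72 and d = 300.**
- Schoenfeld: ½√300 × 0.3285 − 1.96 = 0.885, so power is 81.2%.
- Freedman: √300 × 0.28/1.72 − 1.96 = 0.860, so power is 80.5%.
- A log-rank simulation (762 per arm, stopped at 300 events, 20,000 runs) gives 81.1%.

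The claim of over 80% therefore reproduces at HR 0.72.

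**Step 2: derive the HR from the stated rates.** ln(0.81)/ln(0.75) = 0.7325, which is 0.73 whether rounded or truncated. In reverse, 0.75^0.72 = 0.813, a gain of 6.3 points rather than 6.

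**Step 3: power at the stated rates, d = 300.**
- Schoenfeld: ½√300 × 0.3113 − 1.96 = 0.736, so power is 76.9%.
- Freedman: √300 × 0.2675/1.7325 − 1.96 = 0.715, so power is 76.3%.
- The same simulation gives 76.5%.

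**Step 4: events needed for 80% power.**

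| HR | Schoenfeld | Freedman |
|---|---|---|
| 0.72 | 291 | 297 |
| 0.7325 | 324 | 330 |

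**Step 5: does the plan convert rates to HRs this way elsewhere?** Yes. 90% to 95% gives 0.487 (6.3.2), 85% to 91% gives 0.580 (6.3.3.A, original design) and 87% to 93% gives 0.521 (6.3.3.B, original design). These match the printed 0.487, 0.58 and 0.52. Only the two HRs in the updated MFS calculations do not follow from their percentages.

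**Step 6: the 0 v 6 month comparison.** ln(0.86)/ln(0.80) = 0.676, which rounds to 0.68, against 0.67 printed. At 200 events:

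| HR | Schoenfeld | Freedman |
|---|---|---|
| 0.67 (printed) | 80.8% | 79.8% |
| 0.676 (from rates) | 79.1% | 78.1% |

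At HR 0.676, 80% power needs about 205 to 210 events.

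**The case against.** **The percentages may be rounded displays.** If HR 0.72 was the design input, 81.3% prints as 81% and the power claim stands. The figures are sensitive to such rounding: 74.5% to 81% gives HR 0.716 and 82.5% power, while 75.5% to 81% gives HR 0.750 and 70.3%. This cannot be excluded, and 6.3.3.B does call the 75% approximate. Against it, 6.3.1 frames the target as an absolute 6 points, and the older HRs all follow from their percentages as printed. Even on this reading the text needs reconciling, because the effect powered for would then be 6.3 points.

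**A two-proportion calculation gives over 80%.** Comparing 75% with 81% at 10 years with 762 per arm gives 80.8%. That assumes no censoring and implies 762 × 0.25 + 762 × 0.19 = 335 events, not 300. The named test is the log-rank.

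**The 300 events are not a target.** A reader might infer that the plan will analyse at 300 events and so misses its own target. The documents do not support that. The wording is "Approximately 300 MFS events are anticipated for this analysis", which is a forecast, and the Trial Summary plans assessment by calendar, in 2022. This objection stands in full: the error is in the stated power, not in a stopping rule.

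**The 0 v 6 month comparison.** A reader might also infer that it is underpowered in a way that matters. At 78-79% with about 200 events, it is close to rounding and warrants only a change of wording.

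**Conclusion.** The power statement in 6.3.3.B is wrong as written. Taken at their printed values, 75% to 81% is HR 0.73, and about 300 events give 76-77% power, not over 80%. The chance of missing exactly the 6-point gain is then 23-24%, against about 19% at HR 0.72. The shortfall is small, and 8 to 10% more events than forecast would close it.

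The conclusion assumes proportional hazards, equal allocation, and 75% and 81% read as exact. It does not depend on the choice of power formula: Schoenfeld, Freedman and simulation agree to within one point. The primary outcome, alpha, test, population and recruitment are unaffected.

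**What to change.** In the updated calculation of 6.3.3.B, do one of the following:

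- Print HR 0.73 and state power as about 77% at about 300 events.
- Print HR 0.73 and state that about 325 to 330 events are needed for 80% power.
- Keep HR 0.72 and state the matching 10-year MFS of about 81.3%, a gain of 6.3 points.

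In 6.3.3.A, print HR 0.68 and change the power at about 200 events to about 79%. Section 6.5 refers to a separate, detailed analysis plan that is not in the file. If it repeats these figures, it should be aligned.

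The cost is a few words and a slightly lower stated power, with no extra patients. If the team chose to wait for 80% power in the 6 v 24 month comparison, 24 to 30 more events would be needed. The documents give no MFS event rate. Assuming exponential survival at the stated rates, uniform accrual over 7 to 9 years and no loss to follow-up, events arrive at about 30 a year near 300, so the wait would be roughly 10 to 12 months, or longer with attrition.

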#### 6.3.4 OVERALL SAMPLE SIZE

The overall sample size will depend on how many patients are recruited to both RADICALS-RT and RADICALS-HD, and how many patients join the three-arm Hormone Duration Randomisation. It is anticipated that, of patients who have undergone radical prostatectomy, 10% will have a definite indication for non-randomised early radiotherapy and 50% will have a definite indication for following a non-randomised policy of deferred radiotherapy. The value of early radiotherapy will be uncertain in the remaining 40% who, if they meet the eligibility criteria, should be randomised in RADICALS-RT. No formal overall sample size is estimated, but around 2500 patients will be recruited.

Given the number of radical prostatectomies performed each year in the participating countries, these are feasible target sample sizes.

#### 6.3.5 PILOT PHASE

RADICALS incorporates an 18-month feasibility stage during which randomisation rates, and the trial as a whole, will be carefully assessed. Continuation of the trial beyond the feasibility stage was conditional on satisfactory patient accrual. The trial's progress has been repeatedly reviewed by the TMG, TSC and IDMC as well as the funding body. The decision to review and update the sample size calculations has been taken with full discussion and support, particularly by given the efforts to encourage the accrual. Accrual rates will be monitored throughout the trial.

### 6.4 INTERIM MONITORING AND ANALYSES

Formal interim analyses of the accumulating data will be performed at regular intervals (at least, annually) for review by an Independent Data Monitoring Committee (IDMC, see [Section 15.3](#)). These analyses will be performed by statisticians at the MRC CTU at UCL. The IDMC will be asked to give advice on whether the accumulated data from the trial, together with results from other relevant trials, justifies continuing recruitment of further patients or further Follow-up. A decision to discontinue recruitment, in all patients or in selected subgroups, would be made only if the result is likely to convince a broad range of clinicians including participants in the trial and the general clinical community. If a decision is made to continue, the IDMC will advise on the frequency of future reviews of the data on the basis of accrual and event rates. The IDMC will make recommendations to the Trial Steering Committee (TSC, see [Section 15.2](#)) as to the continuation of the trial.

The trial oversight committees will be asked to continue to monitor and comment on any deviation of the accruing data from the underlying assumptions e.g. higher or lower rates of death from prostate cancer than expected or type of patient randomised.

## **6.5 STATISTICAL ANALYSIS PLAN**

The analyses to be performed for RADICALS will be presented in detail in a separate Statistical Analysis Plan. In short, the main analyses will be performed for patients in RADICALS-RT and separately for patients in RADICALS-HD. The main outcome measures will be compared using the standard time-to-event methods of Kaplan-Meier with formal comparisons using log-rank tests and graphically represented with survival plots. Analyses in the hormone duration comparisons will be stratified by the timing of post-operative radiotherapy (early RT vs deferred RT).

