#### 5.2.2 EFFICACY PARAMETERS

The primary outcome measure is for RADICALS-RT is freedom from distant metastasis. This will be defined as any distant metastasis or death from prostate cancer. Bone scans are not mandated at set times but should be performed as clinically indicated. The primary outcome measure for RADICALS-HD is metastasis free survival, defined as any distant metastasis or death from any cause.

All men should be followed-up for the duration of the trial. With regards to ascertaining causes of death, particular attention will be paid to men who are reported as having died from prostate cancer without previously reporting progression or recurrence, and men who are reported as having died from non-prostate cancer causes after developing hormone refractory disease. There will be a review of causes of death performed independent from allocated trial arm.

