#### 6.2.1 PRIMARY OUTCOME MEASURE - RADICALS-RT

RADICALS-RT was originally designed to detect an absolute improvement of 5% in disease-specific survival at 10-years from 90% to 95% with 80% power. Since the trial was designed in 2006, further information on disease-specific survival in similar patient cohorts has become available from prospective RCTs, including EORTC 22911 (8) and SWOG 8794 (10). These provide useful estimates as they are both clinical trials and recruited partly during the PSA era; such information was not previously available. The results of these trials show that death from causes other than prostate cancer is a major competing risk, with around only one in four deaths being attributed to prostate cancer and a 10-year disease-specific-survival (DSS) of around 94%; this patient cohort is performing much better than had been anticipated originally. With further treatments (e.g. docetaxel) being available and standard of care at the time of relapse and the development of castrate-refractory disease, the time from the development of distant metastasis until death from prostate cancer has lengthened. An absolute improvement of 5% is not a reasonable assumption if these estimates hold true.

However, the role of adjuvant RT remains controversial and a clinical trial is required to resolve this issue. RADICALS-RT will do this. Therefore, focus has turned towards distant metastases, which is an earlier but clinically important and objective outcome measure. The primary outcome measure for RADICALS-RT is now **freedom-from-distant-metastasis**.

Disease-specific survival, therefore, becomes an important secondary outcome measure. At the main analysis of distant metastases, the trial would expect around 41 deaths from prostate cancer and would have 59% power to detect a halving of the risk of prostate cancer death from 6% at 10-years to 3%, ie DSS improves from 94% to 97%. With further follow-up, RADICALS-RT could attain 80% power for DSS after additional 6 years of follow-up (total duration of the trial would be 18.5 years). However, the question of DSS would be addressed sooner through combined analysis with two parallel trials: RAVES and GETUG-17 (see [Section 9.6](#)).

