## 6.3 SAMPLE SIZE

### 6.3.1 BASIC ASSUMPTIONS

The original sample size calculations were performed using the `-art-` package in Stata 9(31). The sample size re-calculation was performed in Stata 11.1. using version 1.0.8 (date 24mar2010) of `-art-`, including `-artsurv-` for the main calculation and `-artpep-` for variations. In terms of accrual and follow-up, we assume 5½ to 6½ years of recruitment, attaining a constant rate of accrual by 3 years after initiation of the trial in RADICALS-RT; a steady rate of accrual may be reached slightly later in time in RADICALS-HD as the rate may not peak until patients allocated deferred radiotherapy in RADICALS-RT start to experience biochemical failure. After recruitment, we assume a further 7 years of Follow-up. Clinically, we assume that, in RADICALS-RT, we should only be interested in treatment options with an absolute increase in 10-year freedom-from-distant-metastasis of 5%. In RADICALS-HD, we should only be interested in treatment options with an absolute increase in 10-year metastase-free survival of 6%, at least.

The sample sizes have been calculated separately for the two randomisations because of potential variation in the underlying assumptions, an uncertain proportion of patients joining RADICALS-RT

and RADICALS-HD and some uncertainty about accrual rates. A number of scenarios relating to trial recruitment and assumptions have been calculated and are reported elsewhere but are available upon request. Selected scenarios are reported here.

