### 6.3.2 RADICALS-RT SAMPLE SIZE

In the patients suitable for this randomisation, the control arm is assumed to be deferred radiotherapy i.e. radiotherapy at PSA relapse.

When the trial was originally designed, there was uncertainty about the likely event rate but it was anticipated that a modest absolute effect in the order of 5% would be required to convince clinicians to adopt adjuvant radiotherapy for all patients. The original sample size calculations anticipated that around 2,600 patients would need to be recruited over 5½ years and followed-up for a further 7 years in order to obtain 80% power to detect an improvement from 70% to 75% or 90% power to detect an improvement from 80% to 85%.

From SWOG 8794 and EORTC 22911, the proportion of patients free of distant metastases at 10 years is estimated to be 90%. We would look to test whether adjuvant RT can improve this to 95% (hazard ratio 0.487), which is seen as the minimum clinically significant improvement required to routinely introduce adjuvant RT to this patient population; this mirrors the size effect observed in SWOG 8794. This is tested using the superiority design. With 80% power, a two-sided 5% significance level, accrual lasting 5½ years (reaching peak accrual rates after 3 years) and a further 7 years of follow-up, we would need to recruit 1,063 patients in order to observe 66 distant metastases events. This sample size assumes that 30% of patients are lost to follow-up and around 30 patients per month randomised from 30 months onward. Therefore, the target sample size will be reduced from 2,600 to around 1,063 patients. This assumes that 30% of patients are lost to follow-up between 5 and 10 years.

If the peak accrual is lower, at around 25 patients per month, accrual would be extended by 1 year, to around 6½ years and around 1,160 patients would be randomised; this should address the question with the same power and in the same overall timescale.

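### Kaplan-Meier is the only estimator named for FFDM, so reported 10-year risks would be modestly overstated; cumulative incidence should be added, with the log-rank test kept

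*Combined protocol and SAP*

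**What the plan says.** Section 6.5 gives a short account of the analysis: "The main outcome measures will be compared using the standard time-to-event methods of Kaplan-Meier", with log-rank tests for formal comparison and survival plots. It begins by deferring the detail: "The analyses to be performed for RADICALS will be presented in detail in a separate Statistical Analysis Plan". That plan is not among the documents. Nowhere does the protocol name a cumulative incidence function or any other competing-risk method.

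Section 5.2.2 defines the RADICALS-RT primary outcome, FFDM: "This will be defined as any distant metastasis or death from prostate cancer". Death from another cause is not an event. Disease-specific survival (DSS) has the same feature, and so does clinical progression-free survival, which counts only prostate cancer deaths (section 6.2.3).

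Section 6.2.1 draws on two earlier adjuvant radiotherapy trials to say that "death from causes other than prostate cancer is a major competing risk, with around only one in four deaths being attributed to prostate cancer". Section 6.2.2 gives other-cause death as one reason for moving the RADICALS-HD primary to metastasis-free survival (MFS), which counts every death.

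The effect of interest is absolute. Section 6.3.1 limits interest to "treatment options with an absolute increase in 10-year freedom-from-distant-metastasis of 5" percentage points. Section 6.3.2 turns this into a design target: "We would look to test whether adjuvant RT can improve this to 95% (hazard ratio 0.487").

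**The concern.** When other-cause deaths are censored, one minus Kaplan-Meier estimates the risk in a hypothetical population in which men cannot die of anything else. It is never below the actual cumulative incidence. The cause-specific comparison of arms remains valid, but the absolute risks and the plotted curves do not describe what happens to patients.

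This matters because the protocol expresses clinical worth as a 10-year absolute gain. Clinicians will read the reported difference as the number of men per hundred spared metastasis or prostate cancer death by treating everyone early. If early radiotherapy is beneficial and other-cause mortality is similar in the two arms, a Kaplan-Meier difference answers that question with too large a figure.

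**Working it through.** **Inputs from the protocol**
- Control-arm FFDM at 10 years: 90% (section 6.3.2). Target: 95%, HR 0.487, two-sided 5%, 80% power, 66 events (same section).
- DSS at 10 years: 94%. One in four deaths is from prostate cancer (section 6.2.1).
- 10-year overall survival in EORTC 22911: 76.9% and 80.7% (section 1.3).

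**Step 1: reproduce the plan's figures**

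HR = ln(0.95)/ln(0.90) = 0.487. Freedman's formula gives events = (1.96 + 0.8416)² × [(1 + 0.487)/(1 − 0.487)]² = 7.849 × 8.402 = 65.9, or 66 as stated.

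For DSS, HR = ln(0.97)/ln(0.94) = 0.492. With 41 events, power = Φ(√41 × 0.508/1.492 − 1.96) = 58.7%, against the stated 59%. Neither calculation involves other-cause death, so neither changes below.

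**Step 2: a range for other-cause mortality**

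The protocol gives no direct figure for this trial. Two routes from its external figures:
- Overall survival of 80.7% to 76.9% means 19.3% to 23.1% dead at 10 years. Three quarters of that is 14.5% to 17.3%.
- A 3:1 ratio of hazards with 94% DSS gives an other-cause hazard of 3 × (−ln 0.94/10) = 0.0186 per year. Other-cause mortality is then 1 − exp(−0.186) = 16.9%, and overall survival is 0.94 × 0.831 = 78%, inside the quoted range.

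The assumed range is 10% to 18%. The lower end allows for mortality below that of the older trials.

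**Step 3: convert to cumulative incidence**

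With constant cause-specific hazards λ (FFDM event) and o (other-cause death):

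CIF(10) = λ/(λ + o) × [1 − exp(−10(λ + o))]

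Control: λ = −ln(0.90)/10 = 0.01054. Early radiotherapy: λ = −ln(0.95)/10 = 0.00513.

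| Other-cause mortality at 10 years | o per year | Control | Early | Difference |
|---|---|---|---|---|
| 0 (Kaplan-Meier scale) | 0 | 10.0% | 5.0% | 5.0 |
| 10% | 0.0105 | 9.5% | 4.75% | 4.75 |
| 15% | 0.0163 | 9.2% | 4.6% | 4.6 |
| 16.9% (3:1 ratio) | 0.0186 | 9.1% | 4.6% | 4.6 |
| 18% | 0.0198 | 9.1% | 4.5% | 4.55 |

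Example, 10% row, control: λ = o, so CIF = 0.5 × (1 − 0.90 × 0.90) = 0.095.

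For DSS, the 3:1 hazard turns 6.0% v 3.0% into 5.5% v 2.7%, so 3.0 points becomes 2.7.

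**Step 4: unequal other-cause mortality**

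Use the survival of each EORTC 22911 arm, with DSS of 94% (control) and 97% (early). Then o = −ln(0.807/0.94)/10 = 0.0153 in control and −ln(0.769/0.97)/10 = 0.0232 in early. FFDM risks become 9.3% v 4.5%, a difference of 4.8. The direction holds here, but the size depends on the balance between arms.

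**The case against.** The strongest reply is that primary inference does not rest on the Kaplan-Meier level. The log-rank test and hazard ratio compare cause-specific hazards validly, and section 6.5 does not list a 10-year difference as an estimate. This stands. A reader might infer that the primary test or its power is compromised; step 1 shows that it is not.

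A reader might also infer that the trial would set an inflated estimate against its 5-point threshold and so wrongly declare early radiotherapy worthwhile. The documents do not support this. The 5 points are a design assumption for a superiority test, and no decision rule uses the estimated difference. The HR of 0.487 is the ratio of log survivor proportions, which places the 90% to 95% target on the net scale. A Kaplan-Meier difference set against it is like for like; a cumulative-incidence difference would not be, unless the target were converted.

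Size is a fair objection too. The shift is 0.25 to 0.45 points. A simple binomial 95% half-width for 10% v 5%, ignoring censoring, is 1.96 × √(0.1375/531.5) = 3.2 points with 1,063 patients, or 2.8 with the 1,396 recruited (698 per arm). The bias is therefore about 8% to 16% of the sampling half-width. The one-in-four split comes from older external trials, and section 6.2.2 reports fewer all-cause deaths than expected in RADICALS-HD. If RADICALS-RT is similar, the lower end is more plausible.

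Two further inferences go too far. The gap would widen with time, but no 15-year estimate is planned; year 15 is only the end of the follow-up form schedule in Table 5. Section 6.5 refers to main outcome measures, so that DSS, now secondary, will be estimated by Kaplan-Meier is an inference. The separate SAP may also already provide cumulative incidence. These points limit the concern but do not remove it: systematic overstatement of reported risk does not shrink with sample size and is easily avoided.

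**Conclusion.** The point holds as a modest, correctable issue in how absolute risk is reported. The only estimator the protocol names for FFDM censors deaths that the protocol itself regards as an important competing event. Overstatement of each arm's actual 10-year risk is general. Overstatement of the benefit is conditional on early radiotherapy being beneficial and on similar other-cause hazards by arm; a large imbalance could alter it.

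At the design values, 10.0% v 5.0% becomes 9.5% v 4.75% to 9.1% v 4.5%, and 5.0 points becomes about 4.75 to 4.55. This rests on constant hazards, on assumed other-cause mortality of 10-18%, and on reading 90% and 95% as net values, as the HR conversion implies. The test, hazard ratio, 66 events and 80% power stand. MFS and overall survival are not affected, since every death is an event in both.

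**What to change.** In the SAP:
- Keep the log-rank test and a Cox hazard ratio as the primary comparison for FFDM, described as cause-specific.
- Report Aalen-Johansen cumulative incidence of FFDM events by arm, with other-cause death as the competing event. Take the 10-year risks, their difference and its confidence interval from it.
- Do the same for DSS and for other secondaries that censor non-prostate deaths (including clinical progression-free survival, and FFDM in RADICALS-HD), unless the SAP already does so.
- Report other-cause death by arm, so that readers can see whether the condition on similar hazards is met.
- State that the 90% to 95% design target is on the net (Kaplan-Meier) scale, so that a cumulative-incidence difference is not judged against an unconverted 5 points.
- Leave MFS and overall survival on Kaplan-Meier.

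The cost is SAP wording and a little extra analysis in standard software. Death report forms are already collected (Table 5), and causes of death are already reviewed independently of arm (section 5.2.2). The reported absolute benefit may be slightly smaller. Outcome assessment was planned for 2022, after this February 2020 version, so the change could be specified in advance.
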